#### Anxiety analysis

2.6.9

The analysis of anxiety will be done through Beck inventory of anxiety that evaluates, by quantitative approximation, anxiety symptoms. The questionnaire contains 21 aspects that reflect somatically, cognitively, and affectively the characteristic symptoms of anxiety. The 21 statements describe the symptoms common in anxiety situations, which should be assessed by the participant with reference to himself or herself, in a 1-week period, on a 4-point scale, reflecting increasing levels of severity of each symptom, whose alternatives are:

(1)Absolutely not;(2)Lightly: It did not bother me much;(3)Moderately: It was very unpleasant, but I could bear it;(4)Seriously: I could hardly bear it.

At the end, the items are summed and the total score can range from 0 to 63. All participants will respond to this questionnaire in the preoperative period and 7 days after surgery.

As anxiety may increase levels of cortisol and inflammatory cytokines adversely affecting the perception of pain and increasing recovery time after surgeries,^[17–21]^ its occurrence will also be evaluated by the immunoenzymatic dosage of inflammatory mediators (interleukin [IL]-1β, IL-6, tumor necrosis factor-α) and cortisol in saliva in the same periods of application of the questionnaire. To do so, participants will be asked to insert a cotton roller under the tongue for 2 to 3 minutes and then this cotton will be removed and placed in a special tube for later laboratory analysis by specific kits. The saliva remaining in the tubes will be discarded in an appropriate place.

### Surgical procedure

2.7

#### Planning and installation of expanders

2.7.1

Before the surgery, all participants will be molded and the respective models of plaster will be mounted in a semi-adjustable articulator, to perform measurements (between the canines and between the molars) and surgical planning. Later, simulation of surgical procedures will be performed in the models with the objective of achieving a stable occlusion and new measures will be performed (between the canines and between the molars). The measurements obtained before and after the simulation will be compared and the difference between them will give the exact measure of the maxillary expansion required.

After the planning stage, a Hyrax type dilator (Dentaurum 602-802; Ispringen, Germany) will be installed on the palate of each participant at least 24 hours before the surgeries. This expander will be fixed by means of orthodontic bands on the premolars and upper first molar of each participant and will not be activated. All expanders will be positioned by the same orthodontist.

#### Surgical procedures (maxillar surgical disjunction [MSD])

2.7.2

The surgical procedures will be performed by 3 surgeons, specialized in maxillofacial surgery. The surgical material and the operative technique will be determined according to the protocol for MSD surgeries of the Maxillofacial Surgery and Traumatology Department of Conjunto Hospitalar do Mandaqui Hospital.

The following procedures will be made in every surgery:

General anesthesia with nasotracheal intubation.Antisepsis of the operative field with alcoholic chlorhexidine 2% in the extraoral region and aqueous chlorhexidine 0.12% in the intraoral region.Placement of sterile surgical fields.Infiltrative anesthesia with 0.5% Bupivacaine with constricting vessel 1: 200,000 (10 mL) at the bottom of the vestibule in the region of the right and left first molar up to the upper canine region.Incision with scalpel blade number 15, extending from the first upper right molar to the first upper left molar.Mucoperiosteal syndesmotomy of the anterior region, exposing the anterior nasal spine and the pyriform aperture, followed for exposure of the canine and zygomatic pillars to the region of the pterygoid lamina.Delimitation of the bone area to be incised (5 mm above the dental apices) with a dry point compass.Osteotomy, with a sagittal saw, in the pyriform opening towards the zygomatic pillar. In the zygomatic pillar region, a reciprocating saw will be used to increase the osteotomy.Osteotomy of the maxillary pterygoid process with a curved chisel, 12 mm wide.Osteotomy of the nasal septum with a chisel.Vertical osteotomy of the anterior nasal spine to the interdental alveolar bone of the central incisors, with a 5 mm wide biselated chisel, directed to the medial sagittal line of the palate.Activation of Hyrax expander (Dentaurum). Surgical access suture with synthetic yarn 3.0 made with polyglactin 370 copolymer (30% glycolide and 70% L-lactide) and calcium stearate (vicryl, ethicon).All participants will receive the following medications in the immediate postoperative period: cefazolin 1 g (intravenous, EV) every 8 hours, dexamethasone 10 mg EV every 8 hours, dipyrone 1 g EV every 6 hours until hospital discharge days).

After hospital discharge, patients will be instructed to take amoxicillin 500 mg (oral tablet) every 8 hours for 7 days, dexamethasone 4 mg (oral tablet) every 8 hours for 3 days, dipyrone 500 mg (oral tablet) every 6 hours for 3 days and mouthwash with 5 mL of 0.1% chlorhexidine digluconate solution, 3× daily. At each return of participants, information will be requested on the amount of medicine ingested.

After the 7-day period, the participant will activate the Hyrax appliance, 1 mm per day (2 activations in the morning and 2 activations at night) until it reaches what was planned in the model surgery. After planned expansion, the device should be locked by the orthodontist for a period of 3 to 6 months.

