### Experimental groups

2.3

Participants will be divided in 2 groups:

PBM group: the participants will receive PBM after surgery.Control group: participants will be attended to in the same way as the PBM group. The responsible for the application of the PBM will simulate the irradiations by positioning the devices in the same places as in the PBM group, but the equipment will be kept off. In order for the participant to not identify the group to which he/she belongs, the device activation sound (beep) will be recorded and switched on at the time of application.

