## Outcome measures

3

All variables will be evaluated by the same 2 examiners, before and after surgery for periods of 1 to 120 days according to each variable. The primary outcomes of the study are: the occurrence and intensity of pain and edema (with evaluation periods of 1, 2, 7, and 14 days after surgery), the occurrence of paresthesia (with evaluation periods of 7, 30, 60, 90, and 120 days after surgery) and bone repair in the anterior palatine suture region (with evaluation periods of 30, 60, 90, and 120 days after surgery). The secondary outcomes of the study are: headache, otalgia, nausea, hematoma, nasolacrimation, nasal bleeding, and surface temperature (with evaluation periods of 1, 2, 7, and 14 days after surgery), dysphagia (with evaluation periods of 7 and 30 days after surgery), anxiety (7 days after surgery), quality of life (with periods of evaluations of 7 and 30 days after surgery), and use of analgesics and anti-inflammatory drugs on the 14th day. Information on gender (male/female), race, age (in years), and educational background (from illiterate to full graduate) will also be collected.^[22,23]^

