### Secondary outcomes evaluation

3.5

The variables: local and systemic temperature, occurrence of headache, otalgia, nausea, hematoma, nasolacrimation, nasal bleeding, and the use of analgesics and anti-inflammatories will be evaluated in the periods of 1, 2, 7, and 14 days after surgery.

The temperature will be measured locally (on both sides) and systemically. The local measurements will be made with an infrared digital thermometer (model TL-612, Techline Comercial Importadora Exportadora e Serviços Ltda, São Paulo, Brazil) in the region of right and left cheeks and anterior nasal spine. The systemic temperature will be measured in the frontal region of the patient, in the median position, 3 cm above the glabella.

The presence of hematoma/ecchymosis will be evaluated by measuring the largest diameter of the colorimetric changes on the right and left side. The measure will be performed by the examiners, who will classify the occurrence of this result into 4 categories:

(1)none;(2)larger diameter smaller than 4 cm;(3)larger diameter between 4 and 10 cm, and(4)larger diameter larger than 10 cm.^[28]^

For the analysis of anxiety, the same questionnaire described for the initial evaluation will be applied 7 days postoperatively. Saliva analysis will also be performed at these same times.

The variables: dysphagia and impact of the procedure on the quality of life of the participant will be evaluated in the periods of 7 and 30 days after surgery.

The evaluation of dysphagia will be performed after 7 and 30 days by questioning and classification on a numerical scale in which:

(0)total absence of dysphagia;(1)dysphagia to solid foods;(2)dysphagia to any liquid or solid food.

The impact of the surgical procedure on the participants’ quality of life will also be evaluated. The examiners will ask the participants to answer yes or no to the following 10 questions, after 7 and 30 days of the surgeries.^[29,30]^

(1)Are you maintaining your social activities normally?(2)Are you working/studying normally?(3)Are you maintaining your normal diet?(4)Do you have difficulty swallowing because of the surgery?(5)Do you have difficulty in tasting food?(6)Can you chew on the sides?(7)Do you have trouble sleeping because of the surgery?(8)Did you have trouble speaking because of the surgery?(9)Has your appearance changed because of the surgery?(10)Do you feel sick from the surgery?

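### Analgesic and anti-inflammatory use is a secondary outcome, but intake under the fixed course given to everyone is not separated from intake beyond it, so the result would be hard to read as drug need (minor)

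*Protocol article*

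**What the plan says.** Three parts of the protocol article bear on this outcome.

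- **The regimen (section 2.7.2).** In hospital it states: "All participants will receive the following medications in the immediate postoperative period". The list includes "dexamethasone 10 mg EV every 8 hours, dipyrone 1 g EV every 6 hours until hospital discharge". After discharge, patients are instructed to take "dexamethasone 4 mg (oral tablet) every 8 hours for 3 days" and "dipyrone 500 mg (oral tablet) every 6 hours for 3 days". No as-needed element is described. Section 2.3 says of the control group that "participants will be attended to in the same way as the PBM group", so the schedule is the same in both groups.
- **The data collected (section 2.7.2).** "At each return of participants, information will be requested on the amount of medicine ingested". Nothing in the article distinguishes doses of the prescribed course from doses taken in addition to it.
- **The outcome.** Section 3 lists as secondary "use of analgesics and anti-inflammatory drugs on the 14th day". Section 3.5 says instead that "the use of analgesics and anti-inflammatories will be evaluated in the periods of 1, 2, 7, and 14 days after surgery".

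**The concern.** The outcome concerns the same two drug classes that the protocol schedules by the clock. A participant who follows the instructions takes the same number of tablets whether or not photobiomodulation (PBM) has eased the pain. The part of intake that responds most directly to need is what is taken beyond the course or after it ends, and the article does not say that this part will be recorded on its own.

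At stake is how the result can be read. If the quantity taken is analysed as a whole, a difference between groups could come from skipped scheduled doses or from additional doses, and the absence of a difference would be just as ambiguous. If the two parts are not recorded separately at the visits, they may not be recoverable later.

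**Working it through.** The article gives no figure for this outcome to reproduce, so the check starts from the schedule.

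**1. Scheduled oral course** (section 2.7.2). Doses = (24 h ÷ interval) × days.
- Dipyrone: (24 ÷ 6) × 3 = 12 tablets; 12 × 500 mg = 6 g.
- Dexamethasone: (24 ÷ 8) × 3 = 9 tablets; 9 × 4 mg = 36 mg.

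**2. Scheduled in-hospital intake, per day** (section 2.7.2).
- Dipyrone: 4 × 1 g = 4 g. Dexamethasone: 3 × 10 mg = 30 mg.
- If these doses are counted, one extra hospital day adds 4 g of dipyrone, which is 4 ÷ 6, or two thirds, of the whole oral course.

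**3. Which assessments fall inside the regimen.** Let discharge be on day *d* after surgery. The fixed regimen then runs to about day *d* + 3.
- Since *d* is at least 0, it never ends before about day 3. Days 1 and 2 are always inside it.
- Day 7 is at or past its end only if *d* + 3 ≤ 7, that is, discharge by day 4.
- Day 14 is at or past its end if discharge is by day 11.
- Length of stay cannot be read from the article text, so the status of day 7 is open. The oral course itself covers 3 of 14 days (21%).

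**4. What pooling would do with full adherence.** Write dipyrone tablets taken after discharge as *T* = 12*a* + *E*, where *a* is the fraction of the course taken and *E* is additional tablets. The group difference in means is

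12 × (difference in mean *a*) + (difference in mean *E*).

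With *a* = 1 for everyone the first term is zero. Assume, for illustration only, mean additional use of 4 tablets in control and 2 with PBM:
- Additional use: 4 versus 2, difference 2, reduction 2 ÷ 4 = 50%.
- Total: 16 versus 14, difference 2, reduction 2 ÷ 16 = 12.5%.

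Adding a constant 12 to every participant leaves the difference, its standard error and any *t* or rank test as they were. Only the percentage changes.

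**5. What pooling would do with variable adherence.** The scheduled part then contributes its own difference (adherence values are assumptions):

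| Adherence in the two groups | Dipyrone tablets of the course | Difference |
|---|---|---|
| 100% and 100% | 12 and 12 | 0 |
| 95% and 85% | 11.4 and 10.2 | 1.2 |
| 90% and 70% | 10.8 and 8.4 | 2.4 |

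On the step 4 assumption of a 2-tablet difference in additional use, an adherence gap of 2 ÷ 12 = 16.7 percentage points is enough to mimic or mask it. The variance also changes: Var(*T*) = 144 Var(*a*) + Var(*E*) + 24 Cov(*a*, *E*). Unless people who skip scheduled doses take more additional ones to a sufficient degree, the total is noisier than *E* alone. The article gives no figure for Var(*a*), so the loss of precision cannot be stated.

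**The case against.** The case on the other side is strong in several respects.

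- **No pooled total is defined.** The article speaks only of use and of asking about the quantity taken at each return. How this becomes an analysis variable may be set out in a full protocol or analysis plan that is not shown. This stands: pooling is a risk here, not a stated choice.
- **The visit times already help.** Assessments on days 1, 2, 7 and 14 split intake by interval. If discharge is by day 4, intake between days 7 and 14 lies after the course. Read literally, the day 14 wording in section 3 may also refer to use after the course. This stands in part. It depends on an unstated length of stay, it does not separate additional from scheduled doses while the course is running, and sections 3 and 3.5 do not agree on the times.
- **Skipping doses is not all noise.** Participants in little pain may stop tablets early, so part of non-adherence reflects need. Because allocation is randomized and participants and examiners are blinded (sections 2.5 and 2.8), skipping unrelated to treatment should balance on average. It adds noise, not bias. This stands.
- **Prescribed intake is worth recording.** It is a co-intervention relevant to pain and edema. This also stands, and it supports reporting it under its own name.

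**Conclusion.** The point holds as a matter of measurement and interpretation. Scheduled intake carries little information on need. At days 1 and 2 it is fixed by the regimen, and within the oral course it departs from 12 and 9 tablets only through missed doses. If scheduled and additional intake are analysed without separation, variable adherence adds noise and ambiguity, as does variable length of stay if in-hospital doses are counted. Illustrative adherence gaps of 10 and 20 points shift the dipyrone count by 1.2 and 2.4 tablets. These gaps and the additional-use figures are assumptions, because the article gives none.

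A reader might infer that the outcome measures only adherence, that it is driven to no difference even if PBM works, or that a group skipping doses would falsely appear to benefit. The documents do not support these readings. With full adherence the mean difference and its test are preserved, missed doses can reflect less pain, and skipping unrelated to treatment is expected to balance under blinded randomization. Nor does the article state a hypothesis that PBM reduces drug need. It lists this as one of many secondary outcomes, so the severity is minor.

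**What to change.** - At each return, record doses of the prescribed course separately from doses taken beyond it or after its end.
- Define the outcome as any use, and number of doses, of analgesics and anti-inflammatories beyond or after the prescribed course up to day 14.
- Report intake of the prescribed course by group, labelled as adherence and co-intervention.
- Reconcile section 3 (day 14) with section 3.5 (days 1, 2, 7 and 14) on when the outcome is assessed.

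The cost is one extra line on information already requested at each return, plus the outcome wording. The drawback is a smaller and more skewed count, which is why the proportion with any additional use should accompany it. The change has to be made at data collection. It leaves the prescribed medication as it is.

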### Procedures to guarantee double blinding (patient and examiners) in the postoperative period

2.8

Once the suture is finished, the researcher responsible for applying PBM will remove and open the envelope containing the experimental group information in which the patient will be inserted and will proceed to the experiment. A single researcher will execute the PBM application and he/she will not perform any type of evaluation. The pre and postoperative evaluations will be done by 2 examiners who will not be aware of the group in which each patient is allocated. Participants will not be aware of whether or not they have received PBM, since the person responsible for the application will position the equipment in the irradiation locations in all participants and will only trigger the light when and where predicted in the specific experimental group. The characteristic sound of the device will be triggered by recording in the control group.

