**Methods::**

A randomized, double-blind, placebo-controlled clinical trial involving 72 participants aged from 18 to 45 years, who search the Department of Buccomaxillofacial Surgery and Traumatology of Mandaqui Hospital Complex, will be conducted. Immediately after surgeries, the participant will be inserted into the placebo or LED group. In the LED group, the participants will receive PBM with an extraoral device (660 and 850 nm with 6 J per point) and an intraoral device (660 nm with 2 J per point) and in the control group the person in charge of the application will simulate the irradiation with the devices kept off. The applications will be in the immediate postoperative period, 1, 2, 7, 14, 30, 60, 90, and 120 days after the end of the surgeries, when the evaluations will also be performed. Facial measurements, extra and intraoral sensitivity, pain and bone repair will be evaluated. Secondarily, data regarding the occurrence of headache; otalgia; nausea; bruising; nasolacrimation; epistaxis; dysphagia; systemic and superficial temperature in the operated region; use of analgesics and anti-inflammatories; anxiety and impact of oral health on the participants’ quality of life will be computed.

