#### Extraoral PBM

2.9.1

Extraoral PBM will be applied with a mask (Cosmedical, São Paulo, Brazil) containing 57 red LEDs and 74 infrared LEDs, in the parameters described in Table 2 and in the periods described previously.

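### The blinding procedures in section 2.8 do not mask the visible red light, a likely though unproven route to participant unblinding that bears mainly on self-reported pain

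*Protocol article*

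**What the plan says.** Section 2.8, headed as the procedures that guarantee double blinding, asserts that participants will not know their group and gives a reason: "Participants will not be aware of whether or not they have received PBM, since the person responsible for the application will position the equipment" on every participant. The same sentence adds that the applicator "will only trigger the light when and where predicted in the specific experimental group". Sound is then handled: "The characteristic sound of the device will be triggered by recording in the control group".

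Section 2.3 describes the sham in matching terms, namely "positioning the devices in the same places as in the PBM group, but the equipment will be kept off", and says that, to keep participants from recognising their group, "the device activation sound (beep) will be recorded and switched on at the time of application".

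On the devices, section 2.9.1 describes an extraoral mask "containing 57 red LEDs and 74 infrared LEDs". The Methods part of the abstract gives the wavelengths: "extraoral device (660 and 850 nm with 6 J per point) and an intraoral device (660 nm with 2 J per point").

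Section 3 makes pain one of the primary outcomes, and section 3.1 has the participant rate it on a VAS and on the NRS-101 at days 1, 2, 7 and 14. Closed eyes are mentioned once, in section 2.6.3, for the sensitivity tests and not for the irradiation.

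**The concern.** The reason offered for blinding contains the feature that separates the arms: the light is on in one group and off in the other. The authors recognised that a sensory cue could reveal allocation and dealt with the sound. The light is an equally obvious cue, and none of the stated measures covers it.

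If participants can tell which arm they are in, their expectations can move their own ratings. Pain is the exposed primary outcome because both instruments are pure self-report. A difference in pain could then reflect belief about treatment as well as any effect of photobiomodulation, and the analysis could not separate the two. Recruiting more participants would not help, since this is bias and not imprecision.

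**Working it through.** The protocol gives no figure on this point to reproduce, so the check sets its statements side by side.

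**Step 1. Cues by arm (sections 2.3, 2.8, 2.9.1 and the abstract).**

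| Cue | PBM arm | Control arm | Equalised by a stated measure? |
|---|---|---|---|
| Device position | In place | In place | Yes |
| Sound | Device beep | Recorded beep | Yes |
| Light | 57 red LEDs in the mask; intraoral device at 660 nm | None, device off | No |
| Warmth, if any | Not described | Not described | Not addressed |

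The protocol itself calls the 57 mask LEDs red, so the visibility of that output is not in doubt. The 74 infrared LEDs are not the issue.

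**Step 2. Sessions at which the light could be noticed.** Section 2.9 lists 8 sessions: immediate postoperative and days 1, 2, 7, 14, 30, 60 and 90. The abstract adds day 120, making 9. The first application follows suturing in an operation done under general anesthesia (sections 2.7.2 and 2.8), so it is set aside. That leaves 8 − 1 = 7 or 9 − 1 = 8 later sessions, with participants presumably awake.

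**Step 3. Later sessions completed before each self-report.** Both session lists agree up to day 90, so the count is the same under either.

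| Rating day | Self-reported outcome | Earlier sessions, excluding the immediate one |
|---|---|---|
| 1 | Pain | 0 |
| 2 | Pain | 1 (day 1) |
| 7 | Pain, anxiety questionnaire, quality of life | 2 (days 1, 2) |
| 14 | Pain | 3 (days 1, 2, 7) |
| 30 | Quality of life | 4 (days 1, 2, 7, 14) |

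Pain on days 2, 7 and 14 is therefore exposed whatever the order of events within a visit. Day 1 is exposed only if pain is rated after that day's application, and the article does not give the order.

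**Step 4. Outcomes largely outside the risk.** Edema is a tape measurement taken by examiners who are stated not to know the allocation (sections 2.8 and 3.2). Bone repair is read from radiographs (section 3.4). Neither depends on what the participant believes.

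**Step 5. Size.** The document gives no expectation effect and no SD for pain, so the bias cannot be derived. For scale only, take 33 per group (section 2.4), a two-sided 5% z test, no true effect, and an assumed shift of *b* SD caused by unblinding. With *s* = *b* / √(2/33) = *b* / 0.246, the false-positive rate is Φ(*s* − 1.96) + Φ(−*s* − 1.96):

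| Assumed *b* (SD) | *s* | False-positive rate |
|---|---|---|
| 0.1 | 0.41 | 7% |
| 0.2 | 0.81 | 13% |
| 0.3 | 1.22 | 23% |
| 0.5 | 2.03 | 53% |

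The conclusion does not rest on any row of this table.

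**The case against.** The strongest reply is that this is a journal article, and that eye protection during facial light treatment is an operational detail which the full protocol may contain. The article does not describe the mask's layout, does not say whether it leaves the eyes exposed, and does not say whether participants close or shield their eyes. The two tables of device parameters are not shown. This stands as a limit on the conclusion. It does not rescue the text, because section 2.8 goes beyond leaving a detail out: it offers a reason why participants will be unaware, and that reason does not cover the light.

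A reader might infer more than the document supports:

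- **That participants will see the light, so blinding has failed.** Nothing shows that the light reaches their eyes.
- **That no eye cover is used.** The article is silent, and silence in a condensed report is not evidence of absence.
- **That allocation is visible for all four pain ratings.** The day-1 rating may come before the first later session.
- **That every primary outcome is compromised.** Edema and optical density are largely insulated. The sensitivity tests are done with eyes closed and seek perceptual thresholds, and anxiety is also assessed through salivary cortisol and inflammatory mediators.
- **That the examiners are unblinded.** Section 2.8 states that they do not know the allocation and that the applicator does no evaluations. A participant who guessed could tell them, but that follows from the participant risk and is not a separate flaw.

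**Conclusion.** The point holds in a limited form. As written, the procedures in sections 2.3 and 2.8 equalise position and sound but not the visible red light, so the stated reason does not support the claim that participants will be unaware of their group. Unblinding is a likely risk and is not established. It bears mainly on self-reported pain at days 2, 7 and 14, conditionally on day 1, and also on quality of life and the anxiety questionnaire.

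This rests on two assumptions: participants are awake at the sessions from day 1 onward, and no unreported cover blocks the light. If opaque covers are already worn in both arms, saying so settles the main point. No bias estimate can be drawn from the document.

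**What to change.** State in sections 2.3 and 2.8 that all participants in both arms wear identical opaque eye covers, fitted before the device is positioned and removed after it has been taken away. If this is already done, confirm it there. If it cannot be done or confirmed, qualify the double-blind description so that it does not extend to self-reported outcomes, and interpret the pain results accordingly.

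Optionally, record each participant's guess of allocation. The guess should be reported with caution, because a participant who feels better may guess the active arm for that reason alone.

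The cost is a set of covers and, if the guess is recorded, one question. No extra visits or staff are needed, and the irradiation itself does not change. Any sensation of warmth from the active device would remain unmasked. The covers help only if they are in place before participants are treated.
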